#### Identification, notification, and referral

2.6.3

Facility stillbirths will be recorded by nurses in labour room registers, case sheets, and MCP cards, and the ASHA will be notified within 24 h via SMS. For home deliveries, the ASHA will directly register the event. Following notification, the ASHA will initiate the first contact. If a home visit is not feasible, the ANM or facility nurse will assume responsibility for the initial contact.

At each contact, ASHAs will assess for predefined physical and emotional red flags using operational definitions provided in the ASHA Job Aid and covered during training. Physical red flags include heavy vaginal bleeding (soaking ≥ 2 pads per hour for two consecutive hours or clots larger than a 50-paise coin); fever (≥38 °C or feeling hot to touch with rigors); wound complications (pus, suture dehiscence, or foul-smelling discharge); breast complications with fever suggesting mastitis; and seizures. Emotional red flags include: suicidal ideation, assessed at every contact using a scripted Hindi-language probe and defined as any affirmative response or spontaneous expression of wish to die or self-harm; severe or persistent distress, defined as inability to eat or drink for >48 h, inability to sleep for >2 consecutive nights, or complete social withdrawal; and acute confusion, defined as disorientation to time, place, or person.

On identification of any red flag, the ASHA calls the CHO immediately, with an expected response within two hours. If the CHO is unreachable within 30 min and the situation is acutely life-threatening, the ASHA activates the national ambulance service (112) directly. Emotional red flags without immediate safety risk are managed through CHO-coordinated psychiatric referral within 24 h. Cases requiring specialised care will be referred to higher-level facilities, including district-level psychiatric services for complex emotional conditions.

All red-flag events, referral actions, and outcomes are documented in the C-COMPASS register column. All operational definitions, the scripted self-harm probe, the referral decision algorithm, and expected response times are addressed during the mandatory full-day ASHA training through didactic instruction and role-play scenarios, and fidelity to red-flag documentation is assessed monthly through the CHO supervision checklist.

Early neonatal deaths will be identified through the same facility-based notification pathway.

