#### Reporting, documentation, and ASHA training

2.6.4

ASHAs will document the stillbirth notification date, visit dates, support provided, red flags identified, and referrals made in an additional C-COMPASS column integrated into existing ASHA registers.

CHOs will compile and report monthly summaries, including total stillbirths, number counselled, and number referred, to the Primary Health Centre (PHC). These indicators will be incorporated into routine postnatal care (PNC) reporting systems, requiring no additional data platform.

ASHA training will be conducted as a structured half-day session covering the 3-Circle Healing Model, use of scripted counselling approaches (including direct enquiry for self-harm), identification of red flags, referral pathways, and documentation procedures. Training will be delivered by CHOs across both intervention blocks prior to implementation.

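### Section 2.6.3 makes a direct ambulance call conditional on the CHO being unreachable within 30 minutes, even when the woman's life is in immediate danger

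*Protocol article*

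**What the plan says.** Section 2.6.3 (Identification, notification, and referral) lists the red flags that the ASHA checks at each contact. Five are physical: heavy bleeding, fever, wound complications, febrile breast complications and seizures. Three are emotional: suicidal ideation, severe or persistent distress, and acute confusion. The two most plainly time-critical physical flags stand at either end of the physical list: "Physical red flags include heavy vaginal bleeding" opens it and "breast complications with fever suggesting mastitis; and seizures" closes it.

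The section then sets the order of action.

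- General rule: "On identification of any red flag, the ASHA calls the CHO immediately, with an expected response within two hours".
- Ambulance rule: "If the CHO is unreachable within 30 min and the situation is acutely life-threatening, the ASHA activates the national ambulance service (112) directly".
- Less urgent emotional flags: "Emotional red flags without immediate safety risk are managed through CHO-coordinated psychiatric referral within 24 h".

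The same section says that "the referral decision algorithm, and expected response times are addressed during the mandatory full-day ASHA training". Section 2.6.4 adds: "Training will be delivered by CHOs across both intervention blocks prior to implementation".

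**The concern.** The general rule applies to any red flag and exempts none. The sentence written for the worst case is the one that contains the wait: it joins two conditions with *and*, so a life-threatening situation is not enough by itself to trigger the ASHA's own call to 112. The CHO must also have been unreachable for up to half an hour.

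For a convulsing or heavily bleeding woman that order is the wrong way round. An early ambulance call costs little, and a late one can cost a great deal. Three features of the plan add weight.

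- One of the two bleeding criteria already requires heavy pad soaking sustained over two hours, so a woman flagged by that route has been bleeding for some time before the 30-minute window opens.
- Three of the five contacts in Table 1 are by telephone (within 72 h of discharge, Day 7 and Day 42). On those contacts the ASHA is not with the woman, and summoning an ambulance is one of the few useful things she can do.
- The 24-hour psychiatric route covers only emotional flags that carry no immediate safety risk. An imminent risk of self-harm therefore falls back on the same CHO-first rule.

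**Working it through.** No sample-size, power or error-rate figure is involved. The check is a reading of the rule, branch by branch.

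**Inputs, all from Section 2.6.3**

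- Listed red flags: 5 physical + 3 emotional = 8.
- Flags stated to be exempt from calling the CHO first: 0.
- Expected CHO response: two hours, for any red flag.
- Conditions for a direct 112 call: (a) CHO unreachable within 30 minutes, and (b) situation acutely life-threatening. Both are required.

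The count of 8 shows only that the rule has no exceptions. For most of the eight, such as a wound problem or persistent distress, calling the CHO first is reasonable. The problem lies with the few flags that can be immediately fatal.

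**The branches for an acutely life-threatening event**

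| Branch | What the article states | Wait before 112 is called |
|---|---|---|
| CHO cannot be reached | ASHA calls 112 once both conditions hold | up to 30 min |
| CHO is reached | Two-hour expected response; no ambulance step or time | not stated |
| 112 called in parallel with the CHO (not in the article) | – | 0 min |

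In the first branch the avoidable delay is at most 30 − 0 = 30 minutes.

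In the second branch the article does not say who calls the ambulance. The word *directly* in the ambulance rule suggests that activation otherwise goes through the CHO. The delay might be no longer than one telephone call, but nothing in the text caps it. The two-hour figure is a general response time and should not be read as an ambulance time.

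**Is there another route elsewhere?** Table 1 mentions red-flag screening and referral but no ambulance step. Section 2.6.4 covers documentation and training content. Section 2.15 sets out immediate escalation for a non-zero answer to EPDS item 10, but that belongs to the study nurse at the Day 60 assessment, not to the ASHA's contacts. The rule in Section 2.6.3 is therefore the only trigger for a direct 112 call that the article states.

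**Frequency.** The expected number of delayed calls would need the rate of life-threatening red flags during ASHA contacts and the proportion of calls in which the CHO is unreachable. The article gives neither, so no count is offered.

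**The case against.** The best defence is that the article condenses a longer pathway. It points to an ASHA Job Aid and a referral decision algorithm, neither of which is shown, and step-by-step emergency triage normally belongs in such documents. On this view the 30-minute sentence is a backstop: try the CHO, and never keep trying for longer than that. It does not forbid an earlier call to 112. The exposure is also narrow. It needs an emergency during a contact, a CHO who cannot be reached, and an ASHA who follows the sentence to the letter. Control blocks have no such pathway at all, so even an imperfect rule adds to routine care.

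Part of this stands. An earlier call is not prohibited, the unseen documents may be safer than the printed text, and it cannot be said that participants will in fact be delayed. The count of eight flags should not be taken as a measure of harm.

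The defence does not dispose of the point. The article did not leave this detail to the Job Aid: it states a trigger and a number and applies them to situations that it calls acutely life-threatening. If the Job Aid differs, the article misstates it. A sequence taught by role-play has to be safe when followed literally, and the study sets out to assess fidelity to a structured protocol. That the pathway improves on routine care does not justify a poor order of steps within it.

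**Conclusion.** The concern holds. As printed, Section 2.6.3 puts a call to the CHO, and up to 30 minutes of trying to reach the CHO, ahead of the ASHA's own ambulance call in an acutely life-threatening situation. The avoidable delay is up to 30 minutes when the CHO is unreachable and unspecified when the CHO answers.

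This rests on the article's wording alone and assumes that the ASHA follows the rule as written. The Job Aid and referral algorithm could already provide for an immediate call. The frequency is unknown. The point is one of participant safety and has no bearing on power, the estimand or the analysis model. It should be corrected because the rule is to be taught to ASHAs, and because Section 3.2 envisages scale-up to all six Palwal blocks and presentation at national level.

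**What to change.** Reword Section 2.6.3 so that the ambulance call does not wait on the CHO. For example:

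> *For any acutely life-threatening red flag, such as a seizure, life-threatening bleeding or imminent risk of self-harm, the ASHA calls 112 at once and informs the CHO in parallel. For all other red flags the ASHA calls the CHO first, who is expected to respond within two hours.*

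Check the Job Aid and the referral decision algorithm against this wording and bring all three into line before ASHA training. If training has already taken place, brief the ASHAs again. If the Job Aid already exempts emergencies, only the article needs correcting.

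The cost is one or two sentences, a check of the training materials and possibly a few additional ambulance calls. No new staff, visits, data items or analyses are needed.

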#### Reporting, documentation, and ASHA training

2.6.4

ASHAs will document the stillbirth notification date, visit dates, support provided, red flags identified, and referrals made in an additional C-COMPASS column integrated into existing ASHA registers.

CHOs will compile and report monthly summaries, including total stillbirths, number counselled, and number referred, to the Primary Health Centre (PHC). These indicators will be incorporated into routine postnatal care (PNC) reporting systems, requiring no additional data platform.

ASHA training will be conducted as a structured half-day session covering the 3-Circle Healing Model, use of scripted counselling approaches (including direct enquiry for self-harm), identification of red flags, referral pathways, and documentation procedures. Training will be delivered by CHOs across both intervention blocks prior to implementation.

### Block selection and matching

2.7

Four of the six SHRiSTI-surveilled blocks will be purposively selected: two allocated to the intervention arm (receiving C-COMPASS from May 2026) and two to the control arm (routine postnatal care). Block pairs will be matched based on population size, ASHA density, monthly stillbirth volume from SHRiSTI surveillance, distance to district referral facilities, and absence of any co-occurring community mental health programme.

Women in the control blocks will receive routine postnatal care as currently delivered within the National health mission program, without any C-COMPASS protocol, training, or structured referral pathway. In practice, ASHA postnatal visits in this context are designed for women with live births and focus on newborn care and breastfeeding support; no standardised protocol, training, or referral pathway exists for ASHA-delivered emotional support following stillbirth. Evidence from qualitative research conducted in the same district using a social autopsy lens found that postnatal support for bereaved women is largely informal and inconsistent, with women commonly discharged from facilities within 24–48 h with minimal counselling and returning to home environments where grief is frequently met with social silence or pressure rather than structured acknowledgement (8). No scripted emotional support, self-harm enquiry, lactation suppression guidance, or structured psychological referral pathway is routinely activated following stillbirth in the control blocks. The Tele-MANAS helpline is available as national infrastructure but is not routinely provided to bereaved women in current practice. The control condition thus represents the documented current standard of care in this setting, against which the incremental effect and cost of C-COMPASS will be estimated.

The remaining two blocks, under SHRiSTI project, will be excluded to minimise contamination, address time and resource constraints, and allow their use as potential future comparators.

### Outcomes

2.8

#### Primary effectiveness outcome

2.8.1

The primary effectiveness outcome will be the mean Edinburgh Postnatal Depression Scale (EPDS) total score (continuous, range: 0–30) at Day 60 postpartum (±2 days), measured by an independent study nurse (15). The EPDS was selected as the primary outcome on the basis that the primary target of C-COMPASS is the prevention of pathological depressive disorder following stillbirth, rather than grief resolution *per se*, a longer-term outcome beyond the scope of this first evaluation. The potential overlap between grief and depressive symptoms in the early postpartum period is acknowledged; this is addressed within the study design by the concurrent administration of the Brief Grief Questionnaire (BGQ) as a secondary outcome, enabling exploratory analysis of the relationship between grief and depression constructs in this population. The EPDS has been used in perinatal loss populations and validated in Indian perinatal settings (16, 17), and its use as the primary outcome enables direct comparison with the closest available LMIC analogue and alignment with NHM mental health referral thresholds.

Outcome assessment will be scheduled at Day 60, after the ASHA's Day 42 visit, to ensure a minimum three-day separation between the final C-COMPASS contact and outcome measurement, thereby minimising response priming and maintaining assessor independence. The EPDS captures symptoms over the preceding seven days; thus, administration at Day 60 reflects the post-intervention steady state. This timing is consistent with the original validation of the EPDS at 6–8 weeks postpartum (15).

Where Verbal Autopsy (VASA) is conducted for the same participant, EPDS, SDS, and BGQ will be administered first, preferably on a different day. If same-day administration is unavoidable, outcome measures will be completed prior to VASA to minimise recall-induced emotional bias.

#### Secondary effectiveness outcomes

2.8.2

EPDS ≥ 13 (probable depressive illness), included as a pre-specified binary outcome for policy-relevant interpretation. The study is not powered for confirmatory testing of this threshold; results will be reported with 95% confidence intervals as exploratory evidence (24).Sheehan Disability Scale (SDS) total score (0–30), assessing functional impairment across work/school, social, and family domains (18).Brief Grief Questionnaire (BGQ) score, assessing risk of complicated grief (19).

All secondary outcomes will be measured at Day 60 (±7 days), postpartum by an independent study nurse.

#### Implementation outcome

2.8.3

The implementation outcome will be the 72 h ASHA visit coverage rate, defined as the proportion of eligible women in intervention blocks receiving a first ASHA visit within 72 h of hospital discharge. This will be measured using ASHA registers and CHO supervision records.

This indicator is expected to be a key determinant for policy adoption. The Supplementary Table S1 details the operational definitions, and implementation outcomes assessed for this study.

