## Introduction

1

Stillbirth, defined by the World Health Organization as foetal death at 28 or more completed weeks of gestation, remains one of the most prevalent yet under-addressed outcomes in global maternal and newborn health. An estimated 1.9 million stillbirths occur annually, with over three-quarters concentrated in sub-Saharan Africa and South Asia (1). India alone contributes approximately 460,000 stillbirths each year (2, 3), accounting for nearly one-quarter of the global burden, despite substantial progress in reducing maternal and neonatal mortality over the past decade (2, 3).

**Table 1 T1:** C-COMPASS contact schedule.

Contact	Timing	Mode	Core components
Contact 1: Early follow-up	Within 72 h of discharge	Telephone call (≥10 min)	Emotional check-in; follow-up on lactation/breast health; direct enquiry for self-harm (using scripted probe); red-flag screening
Contact 2: Check-in	Day 7 (±1 day)	Telephone call	Emotional acknowledgement and active listening; guidance on lactation suppression; assess bleeding, fever and breast pain; family engagement; provide Tele-MANAS helpline information ([name]); confirm Day 14 visit
Visit 1: Recovery	Day 14 (±2 days)	In-person home visit	First in-person visit after two telephonic counselling sessions; assess physical recovery and grief; breast health check; **Circle 1-** Heart/Feelings; **Circle 2:** Mind/Positive Thinking; family counselling; initiation of contraceptive counselling; identify and refer red flags
Visit 2: Continued recovery	Day 21 (±2 days)	In-person home visit	Assess recovery; check for physical and emotional signs of grief and breast engorgement; reinforce family support; counsel on pregnancy spacing; identify women needing further support from district psychiatrist
Contact 3: Postpartum review	Day 42 (±2 days)	Telephone call	Postpartum evaluation; follow-up on emotional wellbeing; precise contraceptive counselling; preconception planning; update ASHA registers; **Circle 3-Support** and update ASHA registers.

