### Study population and eligibility

2.5

*Inclusion criteria:* All women residing in the four study blocks who experience a stillbirth (intrauterine foetal death at ≥28 completed weeks of gestation) during the study period, are able to provide informed consent, and are reachable for an ASHA home visit.

*Exclusion criteria:* Women with severe cognitive impairment precluding informed consent, or those who explicitly decline participation.

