#### C-COMPASS comprises four structured contacts across the 42-day postpartum period

2.6.2

Table 2.

**Table 2 T2:** Incremental cost analysis- components, data sources, and collection methods.

Cost component	Unit	Data source	Method of estimation
ASHA time: Contact 1 (≤72 h)	Minutes per case	ASHA self-report (end of study)	Time × imputed hourly rate
ASHA time: Day 7 call	Minutes per case	ASHA self-report	As above
ASHA time: Visit 2 (Day 14)	Minutes per case	ASHA self-report	As above
ASHA time: Visit 3 (Day 21)	Minutes per case	ASHA self-report	As above
ASHA time: Contact at 42 days	Minutes per case	ASHA self-report	As above
ASHA transport cost	INR per case	ASHA self-report	Direct expenditure
Printed materials/IEC	INR per case	Programme records	Procurement records
ASHA training (amortised)	INR per case	District records	Total training cost ÷ 3 yrs ÷ annual cases
CHO supervision time	INR per case	CHO self-report	Time×CHO salary rate
Routine care cost (control arm)	INR per case	Control block CHO records	Existing per-woman postnatal expenditure

**Table 3 T3:** Detailed framework selection processes.

SELECT-IT purpose	TMF selected	TMF not selected	Key attribute rationale	Practical consideration
Guiding identification of determinants (barriers/facilitators)	TDF (Theoretical Domains Framework)	CFIR (Consolidated Framework for Implementation Research)	TDF focuses on individual-level behaviour change, aligning with ASHA delivery processes; however, it does not fully capture system-level barriers. Both frameworks are evidence-based.	The study team has qualitative and implementation science expertise and can be using this TDF.
Guiding design and adaptation of strategies	ERIC Taxonomy (Expert Recommendations for Implementing Change)	Implementation Mapping	ERIC provides 73 clearly defined, operationalised strategies with standardised labels and action verbs, enabling direct application in ASHA training and CHO supervision. It has strong alignment with behaviour change evidence. Implementation Mapping was considered more resource intensive.	ERIC tools are readily available and usable without extensive training. Strategies can be directly linked to determinants identified during co-design.

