### Incremental cost analysis

2.9

An incremental cost analysis will be conducted from the health system perspective to estimate the additional cost of delivering C-COMPASS per woman counselled, compared to routine postnatal care. A full cost-effectiveness analysis will not be undertaken at this stage, as reliable effectiveness estimates and utility-based outcomes (e.g., QALYs or DALYs) are not yet available. The analysis is intended to inform programmatic decision-making by estimating the additional resources required for implementation.

Three cost components will be included.
First, ASHA time costs per case will be estimated based on self-reported time spent on each contact (72 h visit, Day 7 telephone call, Day 14 visit, and Day 42 visit), multiplied by an imputed hourly rate derived from the average monthly ASHA incentive.Second, direct ASHA costs will include out-of-pocket expenditures such as transport and printed materials incurred during service delivery.Third, programme-level costs will include ASHA training costs (trainer time and ASHA participation time, amortised over three years and allocated per expected annual caseload), CHO supervision time, nurse/ANM time for activities and any additional printing or documentation costs.The primary cost metric will be the incremental cost per woman counselled (INR). Secondary cost indicators will include cost per woman screened positive for depression and cost per referral completed. Cost data will be collected using a structured costing tool administered to ASHAs and CHOs at the end of the study period. Routine care costs in control blocks will be estimated to provide comparative context. All costs will be reported in 2026 Indian Rupees (INR), and no discounting will be applied given the short study duration. Findings will be interpreted in relation to existing benchmarks for community-based mental health interventions in low- and middle-income settings to support policy relevance.

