The implementation case for C-COMPASS rests on a single core argument: it is designed to be absorbed into the existing system, not added onto it. India's 1.04 million ASHAs are already mandated to conduct postnatal home visits under the Home-Based Newborn Care (HBNC) programme (10). C-COMPASS converts the visit that ASHAs already make after a stillbirth, currently an unstructured, informal, and inconsistent interaction, into a structured, documented, and evaluated care episode. The marginal resource requirement is a half-day training, a Hindi job aid, and a column in the existing ASHA register. The Tele-MANAS referral pathway ([name]) is already operational national infrastructure. The incremental cost analysis embedded in this study will quantify this argument in INR per woman counselled, the metric that government decision-makers require before considering programme adoption. The incremental cost analysis will determine whether C-COMPASS falls within the ₹200–500 per beneficiary threshold typical of scalable LMIC community health programmes. If C-COMPASS achieves the feasibility threshold of ≥70% 72 h visit coverage across both intervention blocks, it will demonstrate that ASHAs with targeted training can reliably identify and reach bereaved women in the critical early postpartum window, a finding that has direct programme planning implications at state and national level.

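### The 72 h coverage outcome counts a visit that Table 1 schedules as a telephone call, over a denominator limited to women reachable for a home visit

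*Protocol article*

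**What the plan says.** Section 2.8.3 names one implementation outcome, the rate of 72 h ASHA visit coverage; this is "defined as the proportion of eligible women in intervention blocks receiving a first ASHA visit within 72 h of hospital discharge". The feasibility objective in section 2.3.1.2 uses the same term. The Discussion sets "the feasibility threshold of ≥70% 72 h visit coverage across both intervention blocks", and section 3.2 makes reaching 70%, together with a clinically meaningful fall in mean EPDS, the condition for taking a costed scale-up plan to the state and then nationally.

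On the 72 h contact itself, the article says different things:

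- Table 1 gives its mode as "Telephone call (≥10 min") and describes the Day 14 contact as "First in-person visit after two telephonic counselling sessions". The abstract agrees.
- Section 2.6.3 takes a home visit as the default: "If a home visit is not feasible, the ANM or facility nurse will assume responsibility for the initial contact".
- Section 2.9 costs "self-reported time spent on each contact (72 h visit, Day 7 telephone call, Day 14 visit, and Day 42 visit"), naming a visit and a telephone call as different things within one list.

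On the denominator, section 2.5 admits women who, among other conditions, "are reachable for an ASHA home visit".

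**The concern.** A coverage rate needs one numerator event and a denominator that does not depend on the success being measured. Here neither is secure.

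The numerator is a visit, but the contact schedule places a call in that window. ASHA registers record visit dates (section 2.6.4), so whether a call counts could be settled register by register, or after the data are seen. Section 2.8.3 also does not say whether a first contact made by an ANM or facility nurse under section 2.6.3 counts towards an ASHA rate.

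The denominator leaves out women whom an ASHA could not reach at home. The Discussion nevertheless reads 70% coverage as showing that ASHAs can find bereaved women and get to them early. A rate computed after unreachable women are removed cannot carry that claim. Since section 2.8.3 expects the indicator to weigh heavily in policy adoption, its definition should be fixed before the post-intervention period.

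**Working it through.** **1. The plan's own figures.** The 70% threshold has no derivation, so there is nothing to reproduce for it. The expected number of women follows from section 2.12: 9.2 per arm per month × 6 months = 55.2, which the article gives as about 56. At 56 women the benchmark requires 0.70 × 56 = 39.2, so at least 40.

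**2. Numerator: is a visit scheduled within 72 h of discharge?** The Introduction says discharge is often 24–48 h after delivery.

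- Window closes at 24 + 72 = 96 h (Day 4) to 48 + 72 = 120 h (Day 5).
- First in-person visit in Table 1: Day 14 ± 2, so Day 12 at the earliest.

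The two do not overlap. The readings then give:

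| Reading of *visit* | Schedule followed | Qualifying contacts scheduled, of 56 |
|---|---|---|
| In person | Table 1 and abstract | 0 |
| In person | Section 2.6.3 or 2.9 (early visit) | up to 56 |
| Any contact, calls included | Table 1 and abstract | up to 56 |

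The same delivery can therefore pass or fail according to a choice the article leaves open.

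**3. Denominator.** Let r be the share of notified women who are reachable for an ASHA home visit, and c the coverage among eligible women. Taking unreachable women as not contacted within 72 h, coverage among all notified women is r × c. With c = 0.70:

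| r (assumed) | Coverage of all notified, 0.70 × r | c needed for 70% of all, 0.70 / r |
|---|---|---|
| 0.95 | 66.5% | 73.7% |
| 0.90 | 63.0% | 77.8% |
| 0.85 | 59.5% | 82.4% |
| 0.80 | 56.0% | 87.5% |

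The article gives no value for r. Its expected 56 comes from surveillance counts with no deduction for unreachable women, so the sample size section does not supply one either.

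**4. Costing text against Tables 1 and 2.** Table 1 has five contacts: calls within 72 h and on Days 7 and 42, and home visits on Days 14 and 21. Table 2 has five ASHA time rows, among them "ASHA time: Visit 3 (Day 21"). The list in section 2.9 has four and omits Day 21.

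**The case against.** The best reply is that *visit* is used loosely. Sections 2.8.1 and 2.9 both call the Day 42 contact a visit although Table 1 makes it a call, and section 2.6.2 points to Supplementary-level detail only through the tables, while section 2.8.3 refers operational definitions to Supplementary Table S1, which is not shown. This has some force, but section 2.9 contrasts a 72 h visit with a Day 7 call in the same list, section 2.6.3 speaks of a home visit, and a supplement cannot undo a conflict within the main text.

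Several stronger readings are tempting, and the document does not support them:

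- *Perfect delivery would score 0%.* This needs both the in-person reading and Table 1 as the only source of contact. Sections 2.6.1 and 2.6.3 leave room for an early home visit.
- *Every woman the ASHA misses drops out.* Reachability in section 2.5 has no 72 h limit. A woman first contacted late stays in the denominator and counts as a failure; only never-reachable women are lost.
- *63% or 56% is what coverage will be.* Those figures rest on assumed shares.
- *The 70% figure is a formal trial decision rule.* It appears only in the Discussion, and section 2.15 commits to presenting the findings without that condition.
- *The cost metric will leave out a home visit.* Table 2 includes Day 21, so this is a mismatch between text and table.
- *Home births have no clock.* That detail may lie in Supplementary Table S1 and is not pressed.

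The separate penetration measure also counts in the sponsor's favour: section 3.1 promises the proportion of identifiable cases enrolled and a comparison with those not enrolled. It is a partial safeguard, because it does not enter the 70% figure.

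**Conclusion.** The point holds in limited form. That the numerator is inconsistent is certain from the text: the article describes the 72 h contact both as a call and as a visit, and the outcome is worded for the visit. Under one combination of readings, no qualifying contact is scheduled against the 40 needed; under the others, the benchmark can be met.

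The denominator is conditioned on reachability, so as a measure of reaching all bereaved women the rate can only err upward, provided that women not reachable at home were not contacted in the window. The size of that error cannot be computed from the article; over an assumed reachable share of 80–95%, a reported 70% would correspond to 56–66.5% of notified women.

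The EPDS primary outcome and its analysis are unaffected. What is affected is the feasibility claim and one of the two conditions attached to the scale-up plan.

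**What to change.** 1. Reconcile the mode of the 72 h contact across the abstract, Table 1 and sections 2.3.1.2, 2.6.3, 2.8.3 and 2.9. Which mode is right is for the investigators; this review does not choose it.
2. Define the numerator as completion of that Contact 1 by the ASHA, in the reconciled mode, within 72 h. Count ANM or facility nurse back-up contacts separately.
3. Apply the 70% benchmark to all surveillance-notified stillbirths among residents of the two intervention blocks in the post-intervention period. Report the eligible-only rate beside it.
4. Align the list in section 2.9 with Table 2, so that all five contacts, Day 21 included, are costed.
5. Leave trial eligibility as it is. Removing the reachability criterion would change the primary-analysis population, which this point does not require.

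The cost is small. Section 2.6.4 already records notification and visit dates and has monthly totals of stillbirths and women counselled; the registers may need a field for contact mode. The drawback is that reported coverage may look less favourable.
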